#### **11.4.1. Datasets to be analysed, analysis populations**

The patients data will be analyzed as "intention to monitor EEG", i.e.: forming two groups (one of patients allocated to cEEG, the other to those allocated to rEEG). A per-protocol analysis will also be provided for the primary outcome.

According to current experience with a registry of post-cardiac arrest patients (personal observation in CHUV, Lausanne), subjects lost to follow-up represent 1-2% of the cohort. Available data will be used for secondary outcomes, but subjects will be excluded from analysis of the primary outcome.

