| Control Intervention (if applicable):  | Routine video-EEG performed 2 times (20-30 min each) within 30-48 hours.                                                                                                                                                                                                                                                                                                                                                                                                                                                                                                                                                                                                                                                                                                                                                                                                                                                                                                                                                                                                                                                                                |
| Number of Participants with Rationale: | According to a previous estimate, patients with consciousness disorders undergoing cEEG have a 75% survival rate; while patients without cEEG 61%. Using a power of 0.8, an $\alpha$ error of 0.05, and a 2-side approach, 2x174 patients would be needed to detect this significant difference in survival (primary outcome).                                                                                                                                                                                                                                                                                                                                                                                                                                                                                                                                                                                                                                                                                                                                                                                                                          |

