On the one hand, cEEG has a clearly superior sensitivity in uncovering seizures and SE as compared to routine spot video-EEG (rEEG, which typically lasts 20-30 minutes): a seminal retrospective study in an ICU-based population showed that the detection rate doubles from round 50% after one hour of recording to 95% after 48 hours, especially in comatose subjects. Further evidence for the diagnostic yield of cEEG in patients with altered consciousness comes from a study revealing an increased detection rate of nonconvulsive SE after the introduction of cEEG as compared to historic controls with rEEG (monthly detection rates with cEEG  $5.44 \pm 1.33$ ; with rEEG  $2.17 \pm 1.89$ ,  $p=0.002$ ). Nevertheless, cEEG is a time- and resource consuming procedure, requiring skilled technical personnel, regular assessments by electroencephalographers, and ideally the availability of dedicated, portable video-

EEG recording machines that may be connected to the hospital network for out-of-site inspection, as well as specially conceived supplies allowing emergent imaging procedures (e.g., computed tomography- and magnetic resonance imaging compatible electrodes), namely overnight. Practical considerations have emerged in recent years. For example, it seems that a refined analysis of the first part of cEEG may allow stratifying the risk of encountering seizures in the subsequent recording: if no epileptiform discharge is detected in the first 30-120 minutes, the likelihood would be below 5%. Also, the use of automated software allowing the interpretation of compressed EEG seems to clearly improve efficacy in this setting, reducing the time required to analyze a cEEG by 78%, with minimal loss of sensitivity. While large, mostly academic centers in North America have been using cEEG increasingly since the turning of the century, the vast majority of European hospitals - and all Swiss hospitals including university centers - still do not have the resources to apply cEEG to all patients with consciousness impairment in- or outside the ICUs, and therefore, disturbingly, are not complying with the current European guidelines.

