### 7.4 Criteria for withdrawal / discontinuation of participants

Patients who during the intervention period (30-48 hours) will be diagnosed with clinical or electrical seizures or SE (10-12% are expected (Alvarez et al, Clin Neurophysiol, in press)) will exit the intervention but stay in the study and be managed according to best clinical practice. A uniform definition of electrographic seizures (minimum time >10 seconds) and SE (minimum time >5 minutes) will be used: repetitive, rhythmic or periodic discharges or spike and wave patterns occurring at a frequency of <3 Hz together with evolution in frequency, location, or with electroclinical response to anticonvulsants; or occurring at a frequency of >3 Hz. These criteria, as well as interruption of the intervention as per the treating physician will not prevent assessment of the outcomes (only analyzed as "intention to monitor", according to the intervention group allocation).

Furthermore, refusal/withdrawal of consent from the patient or representative represents a mandatory discontinuation of the study.

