#### Control Intervention

Patients randomized to rEEG will be recorded with at least 21 electrodes placed according to the international 10-20 system; occasionally, a reduced montage will be allowed in patients with extensive neurosurgical scars, according to good common practice. Recordings will last between 20 and 30 minutes; two recordings will take place over a period of 24 to 48 hours. Reactivity testing using auditory and nociceptive stimuli will be performed once per recording. Recordings will be visually interpreted by certified electroencephalographers using the 2013 American Clinical neurophysiology nomenclature, as for the experimental intervention, and the interpretation will be communicated within two hours of its completion to the treating team (idem).

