#### **8.5 Data Collection and Follow-up for withdrawn participants**

If participants or representative refuse to give consent, all data collected so far will not be used. However if participants or representative withdraw consent, all data collected so far will be used for the study purposes in order not to compromise the study.

If the intervention EEG is interrupted (please see 8.3), participants will stay in the study and data will be collected at all study time points as planned but analyzed in intention to monitor.

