### 11.4 Planned Analyses

#### Analysis of the outcomes

All analyses will be carried out by a professional statistician. At study completion, the two interventional groups will be compared regarding survival at six months as "intention to monitor" (predefined analysis for the primary endpoint) and "per protocol", adjusted for potential confounders (logistic regressions).

Analysis of each secondary endpoint will be also conducted using univariate and multivariate approaches.

For univariate approaches, frequency tables ( $\chi^2$  or Fisher exact tests, as needed), t-test, Mann-Whitney U, and Kaplan-Meier tests will be applied, as needed.

For the multivariate approaches, stepwise logistic regression models will be performed to identify independent outcome predictors among those found to have a  $p < 0.1$  on univariate analyses. Accordingly, risk-prediction models will be set-up and "Goodness-of-fit" of these models will be evaluated using a Hosmer-Lemeshow test to ensure the quality of calibration. Solid predictors will be used to predict survival and functional outcome at six months in a model. To evaluate the performance of these models, sensitivity, specificity, positive predictive value, negative predictive value, unweighted accuracy (using exact binomial 95% CI), area under the Receiver Operating Characteristic (ROC) curve, and reclassification analysis (Net Reclassification Improvement – NRI) will be calculated .

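### As 7.4 is written, patients who exit because a seizure is detected fall outside the per-protocol mortality analysis, so that set is selected on an event that allocation itself makes more frequent under cEEG

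*Protocol*

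**What the plan says.** The predefined analysis of 6-month survival is by allocated group (intention to monitor). Protocol 11.4 and the synopsis add a per-protocol comparison of the same outcome, and 11.4.1 confirms it: "A per-protocol analysis will also be provided for the primary outcome". The protocol gives no separate definition of the per-protocol set.

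The nearest it comes to one is in 7.4. Patients diagnosed with clinical or electrical seizures or SE during the 30-48 hour intervention "will exit the intervention but stay in the study and be managed according to best clinical practice". Their outcomes are still assessed, but are "only analyzed as 'intention to monitor', according to the intervention group allocation". The same rule covers interruption by the treating physician. Section 8.5 points the same way for an interrupted EEG: "data will be collected at all study time points as planned but analyzed in intention to monitor". Section 7.4 expects 10-12% of patients to be diagnosed in this way and does not give the figure by arm.

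On detection, 3.1 reports from a retrospective ICU study that "the detection rate doubles from round 50% after one hour of recording to 95% after 48 hours". It also cites monthly nonconvulsive SE detection of 5.44 with cEEG against 2.17 with rEEG.

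On the control schedule, 8.1 says "two recordings will take place over a period of 24 to 48 hours", while the synopsis says "Routine video-EEG performed 2 times (20-30 min each) within 30-48 hours". Sections 3.5 and 8.2 also give 30-48 hours for both procedures.

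**The concern.** A patient who exits because a seizure was found has done what the protocol requires, yet 7.4 confines that patient to the intention-to-monitor analysis. Finding seizures is, according to 3.1, mostly what cEEG is for. More such patients should therefore leave the cEEG arm than the rEEG arm, while rEEG patients with the same but undetected seizures stay in. The two per-protocol groups are then no longer comparable by randomisation.

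Section 3.1 also says that seizure burden correlates with prognosis, so the patients removed are unlikely to be of average risk. The logistic adjustment planned in 11.4 cannot restore the balance, because the variable that drives selection is unobserved in those rEEG patients whose seizures were missed.

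At stake is the credibility of the second reported analysis of the primary outcome, which readers would normally take as a check on the first.

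**Working it through.** **1. The plan's own figure.** Survival of 61% vs 75%, two-sided alpha 0.05, power 0.80, pooled variance, no continuity correction (11.2):

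n = [1.96·√(2·0.68·0.32) + 0.8416·√(0.61·0.39 + 0.75·0.25)]² / 0.14² = 173.1, so 174 per arm.

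This reproduces the protocol; power at 174 per arm is 80.2%.

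**2. How many leave.** Let π be the share of patients with seizures and s the share of these detected. The fraction removed is π·s.

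- Base case: π = 0.12 (assumption, using the upper 7.4 figure as prevalence); s = 0.95 for cEEG and 0.50 for two rEEGs (assumption, borrowed from the 48-hour and 1-hour figures in 3.1).
- cEEG: 0.12·0.95 = 0.114, or 0.114·174 ≈ 20 patients.
- rEEG: 0.12·0.50 = 0.060, or 0.060·174 ≈ 10 patients.

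Section 7.4 gives 10-12% as patients diagnosed, not as prevalence. If it is the pooled diagnosed rate, then π = 2·0.10/(0.95+0.50) = 0.138 up to 2·0.12/1.45 = 0.166. The losses become 23-27 of 174 for cEEG and 12-14 for rEEG.

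**3. Spurious difference with no treatment effect.** Let m1 be mortality with seizures and m0 without, the same in both arms. Neither is in the documents; both are assumed.

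Per-protocol mortality = [(1−π)·m0 + π·(1−s)·m1] / (1 − π·s)

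| π | s, cEEG / rEEG | m1 / m0 | cEEG | rEEG | Difference |
|---|---|---|---|---|---|
| 0.10 | 0.95 / 0.65 | 0.40 / 0.31 | 0.281/0.905 = 0.310 | 0.293/0.935 = 0.313 | 0.3 points |
| 0.12 | 0.95 / 0.50 | 0.50 / 0.30 | 0.267/0.886 = 0.301 | 0.294/0.940 = 0.313 | 1.1 points |
| 0.12 | 0.95 / 0.50 | 0.60 / 0.29 | 0.2588/0.886 = 0.292 | 0.2912/0.940 = 0.310 | 1.8 points |

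Each difference favours cEEG.

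The most extreme case examined reads 12% as the pooled diagnosed rate and takes rEEG detection from the 5.44:2.17 ratio (0.95·2.17/5.44 = 0.38). It fixes overall mortality at 32% (midpoint of 25% and 39%) and m1 at 0.60. Then π = 0.181, and per-protocol mortality is 0.262 vs 0.299, or 3.7 points. If m1 equals overall mortality, the difference is zero.

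**4. Against sampling error.** In the base case 154 and 164 patients remain. With mortality near 30%:

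SE = √[0.30·0.70·(1/154 + 1/164)] = 0.051, or about 5.1 points.

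A bias of 1.8 points is about 0.35 SE and one of 3.7 points about 0.7 SE. The design difference is 14 points.

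**5. What the analysis can see.** Suppose cEEG acts only through extra detection (95% vs 50%), with 10% pooled diagnosed (π = 0.138), non-seizure mortality 32% and undetected-seizure mortality 60%. Lowering mortality among detected patients from 40% to 20% moves the intention-to-monitor difference from −1.2 to −2.5 points. The per-protocol difference stays at −1.9 points, because the detected patients are not in it.

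**The case against.** The strongest reply is that the exclusion is inferred. The per-protocol set is nowhere defined, and its definition is commonly left to a statistical analysis plan. The words in 7.4 sit in a sentence whose purpose is to say that early exit does not prevent outcome assessment. Section 8.3 makes the same point, and 8.5 restates the analysis rule, both without the restrictive word. A patient who exits on protocol instruction could be called compliant. That is a fair reading of the intent, but not of the text: a later plan that kept these patients in would contradict 7.4 as it stands.

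The limits on size also stand. The per-protocol analysis is additional, and no sample size or stopping rule rests on it. The mortality inputs are assumed. Exit also follows clinical seizures, which can be recognised in either arm, so the true imbalance may be smaller than modelled.

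A reader might infer three stronger things that the documents do not support:

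- **That everyone in whom detection could matter is dropped.** Missed seizures stay in: in the base case 0.12·0.50 = 6% of the rEEG arm and 0.12·0.05 = 0.6% of the cEEG arm. Other routes by which EEG could alter care, such as imaging, reducing or stopping antiepileptic drugs, and prognostication, remain too.
- **That selection alone is likely to produce a convincing cEEG benefit.** Every bias computed is below one standard error.
- **That early deaths are excluded.** This is only inferred from the 30-hour minimum for cEEG in 8.1. A control patient who dies before the second recording would be equally incomplete.

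The conflict over the control window is real, but it is a separate matter of consistency and adds nothing to the selection argument.

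**Conclusion.** The point holds in a limited form. Followed as written, 7.4 together with 11.4 and 11.4.1 gives a per-protocol mortality comparison selected on a post-randomisation event that the protocol itself expects more often under cEEG, and adjustment cannot repair it.

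Under no treatment effect the distortion is about 0.3 to 1.8 points in favour of cEEG, and up to about 3.7 points under the more extreme assumptions. The standard error is about 5 points. These figures rest on assumed detection rates and on seizure patients dying more often than others; the protocol does not give that mortality. The bias vanishes if mortality is equal and reverses if it is lower.

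The predefined intention-to-monitor analysis is untouched, so nothing here threatens the trial's main conclusion. The change is still worth making, because it is a stated rule rather than a detail left open, and correcting it costs almost nothing.

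**What to change.** 1. In 11.4.1, state that exit required by the protocol because a seizure or SE was detected, and death during the intervention window, count as adherent in either arm, and that these patients stay in the per-protocol set.
2. Amend the restriction to intention to monitor in 7.4 and the matching sentence in 8.5 to agree. Changing 11.4.1 alone would create a contradiction. Patients whose EEG the treating physician interrupts for other reasons can remain outside the set, so it keeps its meaning as an adherence analysis. Patients in whom the intervention never started, or whose eligibility failed on later information, are already covered as dropouts in 11.5.
3. Describe the per-protocol analysis as supportive of the intention-to-monitor result.
4. Separately, reconcile the control-EEG window between 8.1 and the synopsis, 3.5 and 8.2. At present a control patient whose second recording falls between 24 and 30 hours is adherent or not depending on the section read.

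The cost is a few sentences in the protocol and no new data. The downside is that the per-protocol set moves closer to the full set and so adds less beyond the main analysis.

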#### **11.4.2. Primary Analysis**

Analyses of the clinical outcomes at study completion will be performed by the team of PD [name], University Hospital of Basel, delegated by the sponsor-coordinating investigator and using the clinical trial datasets provided by the data management team of the CRC Lausanne according to adequate format requested by the statistics.

#### **11.4.3. Secondary Analyses**

Quantitative EEG analyses at study completion will be performed by the team lead by [name], Inselspital Bern, delegated by the sponsor-coordinating investigator and using the EEG datasets compiled by the same team based on information extracted from coded EEG traces.

#### **11.4.4. Interim analyses**

An interim analysis of the primary outcome will be performed after recruitment of the first 100 patients: if the difference of 14% in survival at six months between the two arms will be met, the study will be interrupted. This analysis will be conducted by the team of the sponsor-coordinating investigator in Lausanne and using the intermediate clinical trial datasets provided by the data management team of the CRC Lausanne.

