## **5. STUDY OUTCOMES**

### **5.1 Primary Outcome**

- Mortality at 6 months (frequency).

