## **6. STUDY DESIGN**

### **6.1 General study design and justification of design**

This will be a multicenter randomized controlled trial assessing prognostic yield of cEEG. While there will be no blinding during the EEG procedure, as this would prove highly impractical in the proposed setting; however, the most important outcomes will be assessed blindly (at 6 month). The study will be carried out in four university hospitals (of the five in Switzerland) and one large regional hospital, located both in the German- and the French-speaking part of the country. An RCT seems the best way to address the primary objective of this study, particularly in terms of minimization of biases.

It is expected to randomize 350 patients over a 2 year-recruiting period. Patients will receive either cEEG or 2 rEEG within the first 48 hours following randomization, and then will be followed up until 6 months after randomization.

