## 9. STUDY ASSESSMENTS

### 9.1 Study flow charts

| Study period                                                                          | Screening / Inclusion | Intervention period | Follow-up |          |                 |                   |
|---------------------------------------------------------------------------------------|-----------------------|---------------------|-----------|----------|-----------------|-------------------|
| Days/Weeks/Months                                                                     | Day 1                 | Day 1-Day 2/3       | Day 3/4   | Day 7    | Week 4 (Day 29) | Month 6 (Day 180) |
| Time (hours)                                                                          | T-5 - T0              | T0 - T48            | T48 - T60 | -        | -               | -                 |
| Visit Window                                                                          | None                  | None                | + 24h     | ± 3 days | ± 4 days        | ± 10 days         |
| Assessments                                                                           |                       |                     |           |          |                 |                   |
| Demographics                                                                          | X              |                     |           |          |                 |                   |
| Admission details (time, reason, hospital service)                                    | X              |                     |           |          |                 |                   |
| Glasgow Coma Scale or FOUR score                                                      | X              |                     |           |          |                 |                   |
| Brain function alteration requiring EEG (Date, time and type)                         | X              |                     |           |          |                 |                   |
| Previous seizures                                                                     | X              |                     |           |          |                 |                   |
| Informed consent                                                                      | X              | X            | X  | X | X        | X          |

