### 11.2 Determination of Sample Size

According to the only available study broadly addressing this issue , patients with consciousness disorders and cEEG have a 25% mortality (corresponding to 75% survival rate) and patients without cEEG a 39% mortality (implying a 61% survival rate). Considering a power of 0.8, an alpha error of 0.05, and applying a 2-sided test, 2x174 patients (348 in total) would be needed to detect a difference of 61% versus 75% in survival ( $\chi^2$  test for independent samples, Stata version 12, College station, TX). This represents a reasonable difference of non-debatable clinical relevance.

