### 11.3 Statistical criteria of termination of trial

There are no stopping rules for individual participants. The discontinuation criteria for patients are the post hoc or proxy consent refusal/withdrawal, only. An interim analysis of the primary outcome will be performed after recruitment of the first 100 patients if the difference of 14% in survival at six months between the two arms will be met, the study will be interrupted.

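### The interim look is triggered by recruiting 100 patients but tests 6-month survival, with no follow-up condition, and its bare 14-point stopping rule is unsound even with all 100 outcomes in hand

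*Protocol*

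**What the plan says.** Two places in the protocol define the interim look. Section 11.4.4 gives the timing, "An interim analysis of the primary outcome will be performed after recruitment of the first 100 patients", and the consequence, "if the difference of 14% in survival at six months between the two arms will be met, the study will be interrupted". Section 11.3 repeats the rule in nearly the same words: "after recruitment of the first 100 patients if the difference of 14% in survival at six months between the two arms will be met".

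The primary outcome (section 5.1) is mortality at 6 months, analysed as a frequency. Section 9.2.1 obtains it by a structured phone interview, and the flow chart in section 9.1 places that visit at day 180 with a window of 10 days either side.

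On pace, section 6.1 says "It is expected to randomize 350 patients over a 2 year-recruiting period", and each patient is followed for 6 months. The synopsis gives 30 months in total, which fits 24 months of accrual plus 6 of follow-up.

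Section 11.2 sets the error rates: "Considering a power of 0.8, an alpha error of 0.05, and applying a 2-sided test, 2x174 patients (348 in total) would be needed".

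The protocol gives no data cut-off for the look. It does not require the 100 patients to have completed six months, does not say how patients with shorter follow-up are counted, does not say whether recruitment pauses, and does not adjust the significance level.

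**The concern.** The event that starts the look (recruitment) and the quantity it tests (status six months later) are half a year apart, and the protocol does not connect them. Two looks about six months apart, resting on very different amounts of data, both fit the text.

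The criterion has its own problem. It is a bare observed difference, equal to the effect assumed in the sample size calculation, with no allowance for sampling error at 100 patients. Correcting the timing leaves the criterion wrong, and correcting the criterion leaves the timing open.

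The rule is worded as binding and is the only statistical stopping rule in the trial. There is no data safety monitoring committee (section 1.6). The sponsor-coordinating investigator's own team runs the look (section 11.4.4), and the randomisation lists may be transferred to that investigator for it (section 6.2.1). An open cut-off therefore lets an unblinded team choose when to look. The stakes are stopping on chance and a final claim that does not carry the stated 5% error.

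**Working it through.** **Inputs.** 350 patients in 24 months (6.1); 6 months of follow-up (6.1); survival 75% with cEEG and 61% with rEEG, two-sided alpha 0.05, power 0.80, 174 per arm (11.2); 1:1 allocation (6.2.1). Even accrual is my assumption and is varied below.

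**The plan's own sample size.** n per arm = [1.960·√(2·0.68·0.32) + 0.842·√(0.61·0.39 + 0.75·0.25)]² / 0.14² = (1.293 + 0.549)² / 0.0196 ≈ 173.1, rounded up to 174. The stated figure is reproduced.

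**Look held when the 100th patient enters.**
- Rate: 350/24 = 14.58 per month.
- 100th patient: 100/14.58 = month 6.86.
- Completed 6 months by then: (6.86 − 6) × 14.58 = 12.5 patients, about 6 per arm. Using day 180 gives about 14, and the visit window gives about 9 to 19.
- Other assumed accrual patterns:

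| Pattern | Completed 6 months, of 100 |
|---|---|
| All accrued in 18 or 20 months | 0 |
| Linear ramp-up over 3, 6 or 12 months | about 10, 12 or 21 |
| Accrued in 30 months | 30 |
| Accrued in 36 months | 42 |

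- A death before month 6 already fixes the status. At 32% mortality (the mean of 25% and 39%), at most 0.32 × 87.5 = 28 of the remaining patients could be known deaths, so about 12 to 40 of 100 have a determined status.

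**Look held when all 100 have reached month 6.**
- Timing: 6.86 + 6 = month 12.9.
- Randomised by then: 12.86 × 14.58 ≈ 187, and 187/350 is about 54%.
- Information: 100/348 = 29% of the planned outcomes, less the 1-2% expected loss.

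**The 14-point rule with no true effect** (exact two-binomial calculation; ranges cover common survival of 61% to 75%).

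| Patients per arm | Either direction | cEEG advantage only |
|---|---|---|
| 50 | 13-18% (16% at 68% survival) | 7-9% (8% at 68%) |
| 6 | 74-77% (76% at 68%) | 37-38% |

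At 50 per arm, SE = √(2 × 0.32 × 0.68/50) = 0.0933, so z = 0.14/0.0933 = 1.50 and two-sided p ≈ 0.13.

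**Overall type I error.** I counted a stop at 50 per arm as a positive finding and otherwise tested at two-sided 0.05 with 174 per arm. At 68% survival, stopping contributes 16.3% and the final test in trials not stopped adds 2.8%, about 19% in total (16-21% across the range). If only a cEEG advantage stops the trial, 8.1% + 3.9% = about 12% (11-13%).

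**A stricter boundary.** Two-sided p<0.001 at 50 per arm needs 3.29 × 0.0933 ≈ 0.31, that is 31 points. Repeating the calculation with this boundary and the final test at 0.05 gives an overall error of 5.0-5.2%.

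**The case against.** The best defence is that "after" recruitment does not mean on the day the 100th patient enters. The same sentence calls the look an analysis of the primary outcome and names survival at six months, which does not exist for a living patient before month 6. Taking the first 100 as the cohort and waiting for their outcomes fits the text.

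That defence stands. A reader might infer that the rule would act on almost no outcome data, and the documents do not support that as a general statement. It holds only if the look is run as soon as recruitment reaches 100. Even then early deaths are known, so it describes completed follow-up and not all mortality information. The 74-77% chance figure belongs to that reading alone.

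Direction is also open. Section 11.1 frames the hypothesis as improvement, whereas section 2.9 lists early evidence of benefit or harm as a reason to stop. Both versions are therefore shown; one direction halves the chance of a false stop.

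That more than half the patients are enrolled by the time 100 outcomes exist follows from a six-month endpoint and is not an error in itself.

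A statistical analysis plan might normally fix the cut-off and the handling of incomplete follow-up. That does not remove the point, because the protocol itself sets both trigger and criterion, twice, and the criterion fails on the most favourable reading.

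**Conclusion.** The point holds in this form. The protocol ties the look to recruitment while testing 6-month survival, and does not say which of two very different looks is meant. Read literally, about 12 of 100 patients would have completed follow-up, a figure that depends on even accrual.

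The problem with the criterion does not depend on that choice. With all 100 outcomes, 14 points corresponds to p of about 0.13 and would be met by chance in 13-18% of trials, or 7-9% if only a cEEG advantage counts. The overall error of 16-21% (11-13% one-directional), against the stated 5%, assumes that a stop is taken as showing a difference, about 50 outcomes per arm at the look, and an unadjusted final test at 0.05. If a stop were not read as evidence of a difference, the error figure would not apply, but the trial could still end on a gap that chance readily produces.

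**What to change.** Amend sections 11.3 and 11.4.4 in the same words:

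1. Run the look once 6-month vital status is known for the first 100 randomised patients.
2. State that recruitment continues meanwhile.
3. Replace the 14-point criterion with a boundary that preserves the overall two-sided 0.05, and state the direction or directions in which it applies. One example is two-sided p<0.001 at the look, about 31 points at 50 per arm, with the final test kept at about 0.05.

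This takes a few sentences in an amendment and no extra data. The cost is that the look comes about six months later than a literal reading would place it, with about 54% of patients already randomised, and that it will stop the trial less often. Waiting for half the outcomes (174) would be more informative but would fall at 174/14.58 + 6 ≈ month 18, with about 261 of 350 (75%) randomised, so there would be little recruitment left to save.
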